##### Sample size

The sample size will be based on the differences in proportion, assuming that 50% households segregate waste in both groups. As we could not find previous literature quantifying the effect of similar kind of intervention in Indian setting, we assumed that in our study the intervention will increase the waste segregation practice in the intervention group by 20% compared to the control group. Given a 5% significance level and 80% power, then the minimum sample size is *n* = 184 per group. Assuming a design effect of 2 to adjust for the clustering effect, with 10% non-response rate and 20% loss to follow-up, the final sample size for each arm will be 425 households (total 850 households).

We have fixed the cluster number as eight. As the required sample size is 850 households, we will recruit 850 households from 8 wards i.e., around 110 households (cluster size) will be recruited from each ward.

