### Study measures

#### Primary outcome measures

Comparison of change in proportion of households practising waste segregation at different time points in the study when compared to baseline, between the intervention and control groups (Difference in differences between the groups). This is a categorical self-reported variable assessed at household level which will be captured by the waste segregation knowledge and behaviour questionnaire. The variable will reflect whether or not the household is segregating solid waste at household level, but will not reflect the accuracy of segregation.Comparison of change in proportion of mis-sorted waste at different time points in the study when compared to baseline between the intervention and control groups (Difference in differences between the groups). This variable will be objectively assessed at group level across intervention and control group by standard waste composition analysis (pick analysis). This variable will reflect the accuracy of waste segregation practices at group level.

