### Database management

The principal investigator will oversee the process of data management. REDCap will be used for database management. Participants will be given a unique participation information number (PIN) to ensure anonymity and data confidentiality. The entered data will be analysed using to appropriate statistical software. Descriptive statistics will include the mean, median, standard deviation and Interquartile range to summarize the numerical variables. Frequencies and percentages will be used for the categorical variables. Student t test will be used to compare means between the groups and chi square test will be used to compare the percentages between the groups. For skewed data, appropriate non parametric tests will be used. ANOVA repeated measures will be used to compare the means across the study periods (multiple time points) within the groups. Factorial ANOVA will be used to compare the means between the groups across the study period (multiple time points). Appropriate post hoc test (Bonferroni test) will be applied. Multi-level modelling (MLM) and Generalized Estimating Equation (GEE) will be done to adjust the clustering effect and to compare the proportions between the groups across the study period. Intention-to-treat analyses will be followed to assess interventions’ effectiveness.

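### Student t, chi-square and factorial ANOVA are named as between-arm tests although eight wards are randomised; at the protocol's own design effect a test ignoring wards errs about 16.6% of the time, not 5%

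*Protocol article*

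**What the plan says.** The Study design section makes the ward the unit of randomisation. The Sample size section fixes eight wards of about 110 households. Under Sampling strategy the wards form four pairs, with one ward of each pair going to each arm, so there are four wards per arm. The sample size is built on "Assuming a design effect of 2 to adjust for the clustering effect, with 10% non-response rate and 20% loss to follow-up" at a nominal error rate described as "Given a 5% significance level and 80% power".

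The analysis methods stand under Database management. Student's t test compares means between groups, and "chi square test will be used to compare the percentages between the groups". For several visits, "Factorial ANOVA will be used to compare the means between the groups across the study period (multiple time points". Repeated-measures ANOVA is planned only within groups. The section then adds that "Multi-level modelling (MLM) and Generalized Estimating Equation (GEE) will be done to adjust the clustering effect", and that these models also serve to compare proportions between the groups over the study period.

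Under Primary outcome measures both primaries are changes in a proportion, compared between arms against baseline. The first is a self-reported yes/no variable per household. The second is mis-sorted waste from pick analysis, of which the protocol says "This variable will be objectively assessed at group level across intervention and control group". The secondary outcomes include waste quantity in mass.

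**The concern.** Households in a ward share local conditions and, in the intervention arm, a small set of volunteers. The t test, chi-square test and factorial ANOVA, as named, treat each observation as independent. Their standard errors therefore describe a trial that randomised hundreds of households, not four wards against four. The design effect of 2 shows that the authors expect the variance to double through clustering, so the sample size and these tests rest on different assumptions.

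The sentence on multilevel models and GEE helps but leaves two gaps. It does not say which result decides effectiveness, so one outcome could carry a naive and an adjusted p-value that disagree. It also leaves in place the explicit assignment of means over time to factorial ANOVA. That affects waste mass, and the mis-sorted fraction if it is analysed as a continuous value. As named, factorial ANOVA ignores the wards and the repeated measurement of the same units. At stake is a false claim of benefit, with confidence intervals that are too narrow.

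**Working it through.** **Inputs from the protocol.** Significance level 5% (sidedness not stated, two-sided assumed); design effect 2; eight wards, four per arm; about 110 households per ward. The protocol gives no error rate under clustering other than the nominal 5%, so there is no figure of its own to reproduce. Its 184 per group and 425 per arm do not enter this calculation.

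**Step 1: the ICC implied by a design effect of 2.** DE = 1 + (m - 1) x ICC. With m = 110, ICC = 1/109 = 0.009. If only 76 households per ward are analysed (425/4 x 0.9 x 0.8 = 76.5), ICC = 1/75 = 0.013.

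**Step 2: a test that ignores wards.** Its standard error is too small by a factor of sqrt(DE), so the true type I error is 2(1 - Phi(1.96/sqrt(DE))).

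- DE = 2: 1.96/1.414 = 1.386, which gives 16.6%. Beta-binomial simulation under the null (40,000 runs; 76, 106 or 110 households per ward) gives 16.3% to 16.4%.

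The protocol states no ICC. The range over assumed values, with 110 per ward, is:

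| Assumed ICC | DE | Type I error, wards ignored |
|---|---|---|
| 0.005 | 1.545 | 11.5% |
| 0.009 | 2.0 | 16.6% |
| 0.02 | 3.18 | 27.2% |
| 0.05 | 6.45 | 44.0% |

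At ICC 0.005 with 76.5 per ward the figure is 9.5%.

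**Step 3: the cluster-adjusted methods on four against four wards (conditional).**

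- GEE with the uncorrected sandwich variance and a z reference: with four clusters per arm the variance is too small by (4 - 1)/4. The error is P(|t6| > 1.96 x sqrt(3/4)) = P(|t6| > 1.697) = 14.1%. Simulation gives about 13.9%, fitted logistic exchangeable GEE 12.8% (1,000 runs, Monte Carlo SE about 1 point), and a difference-in-differences contrast 14.1%.
- Random-intercept multilevel model: about 7.6% with z and about 3% with t on 6 df.
- GEE with a bias-reduced sandwich: about 5.3% with z and 2.3% with t on 6 df.
- t test on the eight ward summaries, 8 - 2 = 6 df: 5.0%.

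**Step 4: factorial ANOVA.** No separate error rate was computed. Ignoring wards acts as in Step 2. Ignoring the repeated visits adds a further error that depends on the within-unit correlation, which the protocol does not give.

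**The case against.** The strongest reply is that the plan does adjust for clustering. The multilevel/GEE sentence gives two purposes: adjusting for clustering, and comparing proportions over time. Both primaries are defined as proportions compared over time, so the sentence plausibly covers both, and the t and chi-square tests may be meant as simple description. The choice of sandwich correction and degrees of freedom is commonly left to an analysis plan or full protocol.

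Much of this stands. A reader might infer that the trial's 5% error rate as a whole becomes 14% to 17% or more. The document does not support that: the 16.6% belongs to the naive tests, while the primaries may well be tested by the adjusted models. A reader might also infer that means get no cluster-adjusted test at all; that is one reading of the sentence, not a stated fact. Nor does the document say that GEE will be run uncorrected with z, and the multilevel model it also names shows much less inflation. Finally, the ICC values of 0.005, 0.02 and 0.05 are assumptions, and group level for mis-sorted waste could mean the 22-household group or the arm.

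What the reply does not remove is that three tests ignoring wards are written down as between-arm comparisons, without being called descriptive or subordinate. That is a stated choice, not an omitted detail.

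**Conclusion.** The point holds for the naive tests. Student's t, chi-square and factorial ANOVA should not carry between-arm inference in this design. At the protocol's own design effect of 2, a household-level test ignoring wards has a type I error of about 16.6%, roughly three times nominal. This assumes a two-sided 5% test, equal ward sizes and a design effect of 2 for the contrast tested. With 110 households per ward the figure is lower below an ICC of about 0.009 and higher above it.

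The small-sample point about GEE (about 14%) and multilevel models (about 8% with z) is secondary and holds only if no correction is used. All figures treat wards as unpaired; pairing on slum percentage would change them only if it explains between-ward variance.

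**What to change.** Under Database management, remove the t test, chi-square test and factorial ANOVA as inferential between-arm tests, or label them descriptive. Repeated-measures ANOVA is planned only within groups and is not part of this change.

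State that one ward-respecting, small-sample-valid analysis is decisive for both primaries and for the continuous secondary outcomes. The simplest is to compute each ward's change from baseline and compare the four intervention wards with the four control wards by a t test on 6 df. This works for the binary outcome, the mis-sorted fraction and waste mass alike.

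If a multilevel model or GEE is kept, name a small-sample correction with t-based degrees of freedom that suits the outcome: Kenward-Roger or Satterthwaite for linear mixed models, a bias-corrected sandwich for GEE. Corrected GEE with t on 6 df can be conservative (about 2%). Say what unit group level means for mis-sorted waste, so that it can be nested within ward.

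The cost is a change of wording and wider intervals. At a design effect of 2, taking standard errors at their true values, the ward-level interval is about (2.447 x 1.414)/1.96 = 1.77 times as wide as the naive one: a factor of 1.41 from clustering and 1.25 from having 6 df.

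### Mixed models and GEE are the only named adjustment for clustering, but with eight wards their usual large-sample tests would exceed 5% unless a few-cluster correction is used

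*Protocol article*

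**What the plan says.** The Sample size section states "We have fixed the cluster number as eight". Under Study design and Sampling strategy, wards are the unit of randomisation. One ward pair is drawn from each of four strata of slum percentage, and the two wards of a pair are split between the arms. That gives four wards per arm in four matched pairs, with about 106 to 110 households in each.

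The analysis text stands under Database management. After t-tests, chi-square tests and ANOVA, which as written take no account of wards, it says "Multi-level modelling (MLM) and Generalized Estimating Equation (GEE) will be done to adjust the clustering effect" and that these models will compare proportions between the arms over time. They are the only stated protection of the primary segregation proportion against ward clustering. No reference distribution, degrees of freedom or small-sample correction is given, and neither model is named as primary.

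The sample size rests on "Given a 5% significance level and 80% power", on "assuming that 50% households segregate waste in both groups", and on the assumption that "the intervention will increase the waste segregation practice in the intervention group by 20% compared to the control group". From these the article concludes "then the minimum sample size is *n* = 184 per group". Clustering and attrition then enter as "Assuming a design effect of 2 to adjust for the clustering effect, with 10% non-response rate and 20% loss to follow-up", leading to 425 households per arm.

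**The concern.** The robust GEE standard error and the Wald z-test of a mixed model are justified when there are many clusters. With four wards per arm, the between-ward variance is estimated on 6 degrees of freedom, or 3 if the pairing is respected. The uncorrected sandwich is also biased downwards. With dozens of wards, silence on this would be harmless. With eight, the choice of inference decides whether the 5% level in the sample-size section holds.

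The stake is the primary comparison of segregation. If the models are fitted with usual large-sample inference, the intervals are too narrow and a false positive is more likely than the stated level. Correct inference needs larger critical values, and the sample-size calculation makes no allowance for them.

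**Working it through.** **Inputs from the article.** Eight wards, four per arm, four pairs; 50% baseline segregation; an increase of 20%, not said to be absolute or relative; 5% significance and 80% power; design effect 2; 10% non-response and 20% loss; 184, then 425 per arm.

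**Assumptions.** Two-sided test, equal ward sizes, follow-up proportions compared rather than changes from baseline. The intracluster correlation (ICC) is not stated. From 1 + (m - 1) x ICC = 2 it is 1/105 = 0.0095 at m = 106 households per ward, or 1/76 = 0.013 at m = 77 (after attrition).

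**The plan's own figure.** n = [1.96 x sqrt(2p(1-p)) + 0.84 x sqrt(p1(1-p1) + p2(1-p2))]^2 / (p2-p1)^2, where p is the mean of p1 and p2.
- 50% vs 70%: 93 per group (103 with continuity correction).
- 50% vs 60%: 388 per group (408 with continuity correction).

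Neither gives 184. Without continuity correction, 184 per group has 80% power for a difference of about 14.5 points. The inflation does not give 425 either: 184 x 2 = 368, and 368 / (0.9 x 0.8) = 511. This is a separate defect. It matters here because the stated 80% has no single effect behind it.

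**Type I error, closed form, k = 4 equal wards per arm.**
- The sandwich variance is (k - 1)/k = 3/4 of the unbiased between-ward variance. Referred to a normal distribution, it rejects with probability P(|t6| > 1.96 x sqrt(0.75)) = P(|t6| > 1.697) = 14.1%.
- A Wald z-test with the unbiased between-ward variance: P(|t6| > 1.96) = 9.8%.
- With pairs as fixed effects: P(|t3| > 1.96) = 14.5% for Wald z. The uncorrected sandwich is then 3/8 of the unbiased variance, so P(|t3| > 1.96 x sqrt(0.375)) = P(|t3| > 1.200) = 31.6%.

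**Type I error by simulation** (beta-binomial, 200,000 runs per setting, no effect, design effect 2):

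| Test | Rejection at nominal 5% |
|---|---|
| Mixed model, REML, Wald z | 7.9% |
| Mixed model, ML, Wald z | 10.4-10.6% |
| GEE, uncorrected sandwich, z | 14.0-14.2% |
| Ward-level t, 6 df | 5.0-5.1% |
| Paired ward-level t, 3 df | 5.0-5.1% |

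The REML figure is below 9.8% because the ward variance is truncated at zero in some runs. It rises to about 10% at an ICC of 0.05-0.10. A further 1,000 fits with a standard GEE routine gave 12.1%.

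**Power of a valid ward-level t-test at design effect 2.** The noncentrality is (p2 - p1) / sqrt([p1(1-p1) + p2(1-p2)] / (n/2)), with n households analysed per arm. The critical values are 2.447 (6 df) and 3.182 (3 df). The lower n is 425 x 0.9 x 0.8 = 306. For example, 50% vs 70% with n = 306 gives 0.20 / sqrt(0.46/153) = 3.65.

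| Comparison | n per arm | Noncentrality | 6 df | 3 df |
|---|---|---|---|---|
| 50% vs 70% | 306 | 3.65 | 86% | 68% |
| 50% vs 70% | 425 | 4.30 | 94% | 81% |
| 50% vs 64.5% | 306 | 2.59 | 58% | 43% |
| 50% vs 64.5% | 425 | 3.05 | 72% | 55% |
| 50% vs 60% | 306 | 1.77 | 32% | 24% |
| 50% vs 60% | 425 | 2.08 | 42% | 31% |

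Power also depends on the ICC. At an assumed 0.05, 50% vs 70% gives 51-53% (6 df) or 37-39% (3 df).

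**The case against.** The best reply is that the article gives one sentence on these models and prescribes no z-test, normal reference or uncorrected sandwich. Such detail is commonly left to a full protocol or SAP, and both model families can be used validly with eight clusters. This stands in part. A reader might infer that the planned analysis does reject at 8-14%. The document supports only that it would do so if fitted without a few-cluster correction. What remains is the combination that the article itself fixes: eight wards, together with methods whose usual inference assumes many.

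A second reply concerns power. A reader might take 2.80 (1.96 + 0.84) as the noncentrality, obtain 65% with 6 df or 48% with 3 df, and conclude that power is below 80% in general. That presumes 184 per group gives exactly 80% for the planned effect, which is so only near 14.5 points. For 50% vs 70% with 184 effective households per arm, the noncentrality is 0.20 / sqrt(0.46/184) = 4.0 and a valid 6-df test has 91% power. This reply stands: a flat 65% is not supported.

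Two further inferences also go too far. A two- to threefold false-positive rate does not fit the REML mixed model, where 7.9-10% is 1.6 to 2 times nominal; only uncorrected GEE comes near three. Nor does the article say that GEE will cluster on household, or that both models are co-primary. It links them to the clustering effect and defines the cluster as the ward.

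**Conclusion.** The point holds as a conditional one. With four wards per arm, the named models under usual large-sample inference would have a Type I error of about 8-10% (mixed model, Wald z) or about 14% (GEE, uncorrected sandwich) at a nominal 5%. Entering the pairs as fixed effects without correction would make it worse. These sizes assume equal wards. The closed-form figures do not depend on the ICC, and the simulated ones use the ICC implied by design effect 2 unless stated.

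On power, the calculation has no allowance for few degrees of freedom, but whether 80% survives depends on the effect and the pairing. It survives for 50% vs 70% with 6 df. With 3 df it fails after the planned attrition and only just holds with all 425 analysed. It fails for 50% vs 60% and at about 14.5 points under either choice.

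**What to change.** Name one primary analysis of the segregation proportion with the ward as cluster and small-sample inference. Either compare ward-level change summaries by a t-test with ward-level degrees of freedom, or use GEE clustered on ward with a bias-corrected sandwich (for example Fay-Graubard or Kauermann-Carroll) and a t reference. State whether it respects the four pairs (3 df) or not (6 df), and make the other model a sensitivity analysis. Settle this before outcome data are seen.

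In the sample-size section, state whether the 20% is absolute or relative, then recompute power with the matching t distribution. Do not replace the 80% by a single 65%.

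The cost is wording, wider intervals and possibly a less favourable stated power. At the same standard error, intervals widen by 2.447/1.96 = 1.25 against z with 6 df, and by 3.182/1.96 = 1.62 with 3 df. Against an uncorrected sandwich the 6-df factor is 2.447/1.697 = 1.44. No extra households or visits are needed for the analysis change.

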### Project Coordination Committee

The Project Coordination Committee (PCC) will be formed for effective coordination, management, planning and implementation of project. The PCC will be comprised of PI and co-investigators. Additional persons may be included, where appropriate The PCC will meet face to face once in a year along with annual meeting. PCC will also be in touch during the entire life of project through telephone, emails and other online meeting platforms.

### Data Collection and Management Committee

Data Collection and Management Committee (DCMC) will be formed. The DCMC will have at least one person from each partner organization having specific responsibility for data collection and management. The DCMC will be responsible for 1) designing study tools, intervention and databases 2) development of protocol for data collection, management, entry and quality check 3) trainings of volunteer and research staff 4) protocol for data storage and documentation (4) Handle all related issues including ethical aspect 5) communication and dissemination.

### Quality control

Will be applied to each stage of data handling to ensure that all the data are reliable and have been processed correctly. The research team will perform source data review and source data verification to confirm that data entered by authorized personnel are accurate, complete, and verifiable from source documents; that the safety and rights of participants are being protected; and that the trial will be conducted in accordance with the currently approved protocol and any other trial agreementsand all applicable regulatory requirements.

## Discussion

Improved solid waste management at all levels is needed to maintain environmental balance amid rapid socio-economic development [42, 43]. Adopting proper waste segregation practices at household level could be the key for developing workable waste management systems in urban settings. Segregation at the source ensures that waste goes through different recycling and resource recovery streams, reducing waste and offering economic opportunities for households and communities [4]. Waste segregation and its proper management can be one of the important determinants of creating healthy, and sustainable communities. In the context of the SDGs, realisation and recognition of effective, improved and adequate waste management levels may be the key, vital driver for attaining environmental protection and improved health and well-being [44].

Waste management in LMICs is highly centralized and the role of community participation in waste management is limited [45]. The existing system usually adopts a legal route of collecting fees or fining for noncompliance to change peoples’ behaviour. The sustainability of behaviour change achieved by such approaches is questionable. Innovative, context-specific, economical, socially acceptable, participatory, simple, evidence-based interventions are needed for developing sustainable waste management solutions [46, 47]. The present study is designed with the concept that an external motivator, who will be the volunteer selected from the own community, empowered with adequate training, could disseminate the information to their community and may promote household waste segregation and ultimately pro-environmental behaviour. The study envisages that the volunteers could act as the link between waste management service providers and the community, give a local perspective to waste management, and help to change community habits through information, and constant communication and feedback. Previous studies have shown that volunteer based education intervention improved environmentally responsible behaviours e.g. recycling at the household level [31, 37, 40, 41, 45, 48, 49]. This technique is believed to work due to individuals being motivated by appearing consistent. This method may also help to other ways of waste management appropriate to context. Building on the results and the experience gained from this study, we could develop better, more efficient interventions to promote pro-environmental behaviour. There are studies suggest that interventions developed with an underpinning of an explicit theoretical foundation are more effective than those lacking a theoretical base [50]. In our study, the intervention content will be developed based on the integrated MOAB model which incorporates the complexity of behaviour and often used to influence waste segregation and recycling behaviour [30, 32]. Thus, we envisage that combining the concept of local volunteer as an external motivator delivering an information developed with an explicit theoretical foundation could be effective.

The objectives of the present study are well connected and relevant to the Government of India’s initiatives of Clean India Mission and development of Smart Cities that aim to develop citizen friendly and sustainable cities across India. This initiative also includes effective waste segregation and management systems in urban communities as a focus [51]. The findings of this project will add to understanding of households’ compliance and challenges of waste segregation. The results of the proposed intervention to improve waste segregation can be replicated in neighbourhood clusters and similar settings on a broader scale. The project processes and results may add social value contributing to improved health and well-being [41].

